## Abstract

**Background:**

Non-alcoholic fatty liver disease (NAFLD) represents a spectrum of disease ranging from simple fatty liver to non-alcoholic steatohepatitis, cirrhosis, liver cancer and liver failure. NAFLD affects up to 30–40% of adults in Western countries and is directly linked to overweight and obesity. There are no approved drugs to specifically target NAFLD, therefore weight loss achieved through changes in dietary and physical activity behaviours is the recommended management approach. However, achieving and sustaining weight loss is challenging for patients with NAFLD. We developed a NAFLD-specific digital lifestyle intervention (VITALISE) to target changes in dietary and physical activity behaviours of patients with NAFLD to initiate weight loss and weight loss maintenance. This study aims to evaluate the feasibility and acceptability of VITALISE in a secondary care clinical setting.

**Methods:**

A single-centre, one-arm, prospective design will be used to assess the feasibility and acceptability of recruitment, uptake, engagement and completion of VITALISE. Health-related outcomes will be assessed at baseline and 6-months. An interim measure of self-reported weight, physical activity and self-efficacy will be recorded at 12-weeks. Qualitative semi-structured interviews conducted at 6 months follow up will further explore acceptability and feasibility and fidelity of receipt and enactment. The study aims to recruit 35 patients with newly diagnosed NAFLD over a 6-month time period. Eligible patients will have continuous access to VITALISE and monthly tele-coaching support for 6 months prior to follow-up with a hepatologist.

**Discussion:**

VITALISE offers access to evidence and theory-informed tailored dietary and physical activity support for patients with NAFLD. The intervention is designed for use by patients in their own time, outside of the hospital setting to overcome well documented challenges including attending additional appointments, and lack of time during routine appointments to adequately address lifestyle behaviour change. This feasibility study will determine the feasibility of VITALISE to support clinical care delivery.

**Trial registration:**

ISRCTN12893503.

## Introduction

Non-alcoholic fatty liver disease (NAFLD) affects up to 30–40% of adults in Western countries and is the most common liver condition worldwide [1, 2]. It represents a spectrum of liver disease ranging from simple fatty liver through to non-alcoholic steatohepatitis (NASH – liver inflammation), life threatening cirrhosis, liver cancer and liver failure, and has become a common cause of liver transplant. Approximately 40% of patients with NAFLD will develop progressive liver fibrosis and ultimately, 5–11% will develop end-stage liver disease [3, 4].

NAFLD is directly linked to being overweight or obese, usually caused by chronic excess calorie consumption and a lack of physical activity and exercise [5]. Currently, there are no approved drugs to specifically target or treat NAFLD. Weight loss, achieved through change in dietary and physical activity behaviours is the recommended treatment for NAFLD, which can reduce liver fat, inflammation and fibrosis [6, 7]. Evidence-based clinical guidelines for the management of NAFLD state the importance of lifestyle behaviour change in patients with NAFLD, regardless of disease severity [8–10]. However, people with NAFLD find achieving sustained weight loss a significant challenge, and clinicians struggle to support patients with NAFLD due to a lack of specific training, interventions, and referral pathways [11–13].

We systematically developed an evidence and theory-informed NAFLD-specific digital lifestyle intervention using Intervention Mapping [14]—VITALISE (inter**V**ention to promote l**I**fes**T**yle change in non-**A**lcoholic fatty **LI**ver disea**SE**) [15]. Intervention Mapping provides a systematic approach to developing theory- and evidence-informed interventions that integrates the requirements of the target population [14]. It provides a step-by-step account of the translation of theory- and evidence-based behaviour change techniques into intervention components, which explicitly target theoretical determinants of behaviour and behaviour change [14]. This process enables replication in terms of development and delivery of interventions and facilitates intervention optimisation and robust evaluation. VITALISE was co-designed with patients and healthcare professionals (HCPs) and addresses the pressing need for a behaviour change programme for people with NAFLD, targeting dietary and physical activity behaviours to initiate weight loss and weight loss maintenance. It provides guideline-recommended structured education and self-regulation tools to facilitate supported self-management. Together these enable patients to plan and track changes, and develop strategies to overcome any barriers encountered, supported by lifestyle coaches.

## Aims and objectives

The aim of the study is to evaluate the feasibility and acceptability of VITALISE in the clinical setting within secondary care. This feasibility study will not include formal hypothesis testing because it is not powered to detect clinically meaningful changes in outcomes. The main aim is to gain insight into whether patients find VITALISE acceptable and whether it is feasible to deliver within routine clinical care.

In accordance with NIHR and CONSORT guidance for feasibility studies [16, 17], the primary objectives are to determine recruitment, retention and attrition rates, intervention uptake, engagement, adherence, and follow-up rates and to test the robustness of our data collection procedures. We will collect data on usability and individual patient views on VITALISE via semi-structured interviews to add important context to quantitative outcome data. Importantly, we will look at the demographics of patients who participate versus those who decline. We will seek information from those who decline to explore ways in which these barriers to participation can be overcome.

The secondary objective is to determine whether participation in the intervention leads to changes in outcomes including physical activity, diet, body weight, HbA1c, liver enzymes, liver stiffness, blood pressure, lipid profile (all measured as part of standard care using the NAFLD Care Bundle) [18] and patient activation/empowerment. These preliminary data will provide some indication of whether the intervention could be effective as part of routine clinical care.

## Methods

### Study design

This feasibility study will use a single-centre (Newcastle upon Tyne Hospitals NHS Foundation Trust (NuTH)), one-arm, prospective design. Feasibility and acceptability of recruitment, the intervention (VITALISE), and associated outcome measures will be assessed using a mixed-methods approach. Health-related outcomes will be quantitatively assessed at baseline and 6-months. An interim measure of self-reported weight, physical activity and self-efficacy (via the Patient Activation Measure (PAM)) will be recorded at 12-weeks.

### Sample size

With reference to best practice guidelines on sample size requirements for feasibility studies [19] and practical time frames, we will aim to recruit 35 patients over a 6-month time period.

### Target population

Adults with newly diagnosed NAFLD (see inclusion criteria for definition).

### Patient identification and consent process

Patients will be recruited from the Liver Unit at NuTH. Eligible patients will be given/sent a study invitation letter and participation information sheet. At the clinic visit, the treating physician will discuss the study with eligible patients following receipt of standard NHS care (i.e. review, examination, and blood tests). If the patient is interested in taking part, a research team member will provide them with more information about the study, answer any questions, obtain written informed consent, collect baseline data, and offer an induction to the intervention (either on the same day as the clinic appointment, or on an alternative day if preferred by the patient).

#### Inclusion criteria

• Aged over 18 years• Clinical diagnosis of NAFLD following review by a hepatologist within the last 6-months• Willing and able to provide written informed consent

#### Exclusion criteria

• Decompensated NASH cirrhosis (Child Pugh score ≥ 7)• Diagnosed/previous eating disorder or purging as recorded in the medical notes• Potentially harmful alcohol consumption (>14 units/week for females; >21 units/week for males)• Known cancer (except skin cancer)• Myocardial infarction within 6 months or uncontrolled cardiovascular disease• Pregnant/considering pregnancy• Inability to read and converse in English

### Preparation procedures

A member of the research team will use a study-specific medical questionnaire to collect sociodemographic and clinical data including information on medical history and current medications (See supplementary file). Body weight, height, waist and hip circumference, blood pressure, blood tests (glucose, lipid profile, liver blood tests [LBTs], full blood count [FBC], HbA1c), liver stiffness measurement [LSM] by Fibroscan and calculation of clinical scores (QRISK^3^, Fibrosis-4 (FIB-4) Score, NAFLD Fibrosis Score (NFS)) will be measured as part of standard care. Patients with Type 2 diabetes (T2DM) will be monitored as part of standard care and medications adjusted in response to weight loss/dietary change/physical activity as necessary. This will be reported as part of the evaluation.

Patients will be asked to complete a physical activity questionnaire (the Godin leisure-time physical activity questionnaire [20]) and Patient Activation Measure (PAM) [21] as part of the research study at baseline, 12-weeks and 6-month follow-up. Patients will also be given an accelerometer to wear for 7-days (to objectively measure physical activity levels) which will be returned to the research team in a pre-paid envelope at baseline and 6-month follow-up.

VITALISE has been developed in collaboration with a commercial organisation, ‘Changing Health Limited’, who are a leading provider of lifestyle behaviour change programmes to the NHS (Changing Health | Digital Behaviour Change At Scale). Changing Health provide evidence-based education and lifestyle coaching digital solutions for people with type 2 diabetes across the UK and renders its innovative services customised to their clients’ requirements. With the patient’s permission, the research team will send their email address, and full name to Changing Health who will subsequently email the patient a welcome email allowing them to access the VITALISE intervention and setup their profile. A researcher will provide patients with a demonstration of how to login to VITALISE. Table 1 outlines the summary schedule of investigations.

**Table 1 Tab1:** Summary schedule of investigations: (* = completed as part of standard care). Patients will be asked to self-report their weight, physical activity levels and complete the PAM at 12-weeks. This interim “visit” will be conducted by telephone

Visit	1	2 (Virtual)	3
**Timescale**	**0**	**12-weeks**	**6-months**
**Study Procedure**			
Review inclusion/exclusion	X		
Obtain informed consent	X		
Height*	X		
Weight*	X	X	X
Waist and hip circumference*	X		X
Blood pressure*	X		X
Fibroscan* (LSM^1^, IQR/med ratio^2^, CAP^3^ and CAP IQR^4^)	X		X
Bloods: Glucose*, Lipid profile*, LBTs^5^*, FBC^6^*, HbA1c^7^*	X		X
Calculation of: QRISK3^8^*, FIB-4^9^*, NFS^10^*	X		X
Physical activity: Step count Accelerometry (7-days)	X X	X	X X
Questionnaires: PAM Score^11^, Godin Physical Activity	X	X	X
Semi-structured interview			X

^1^Liver stiffness measurement

^2^Interquartile range/median ratio

^3^Controlled attenuation parameter

^4^Controlled attenuation parameter interquartile range

^5^Liver blood tests

^6^Full blood count

^7^Glycated haemoglobin

^8^Cardiovascular disease risk score

^9^Fibrosis-4 Score

^10^NAFLD Fibrosis Score

^11^Patient Activation Measure

### Intervention

Patients will be given a personal login for VITALISE and will have continuous access for a 6-month period prior to their follow-up appointment with a hepatologist. They will be supported by monthly personalised tele-coaching sessions delivered by specifically trained lifestyle coaches. A pedometer will be provided to allow patients to record daily step count. Table 2 provides and overview of VITALISE content.

**Table 2 Tab2:** Overview of VITALISE content: to be added into page 9 under table 2 heading

Module	Sub-components	Description of information content
**Module 1: Introduction**	**Welcome to VITALISE with Changing Health**	Message from a specialist in lifestyle management of NAFLD providing an overview of the aims and objectives of the programme
**Module 2: Understanding non-alcoholic fatty liver disease (NAFLD)**	**What is NAFLD?**	Overview of the liver; what is NAFLD and how it progresses; the different stages of the disease
	**How is NAFLD diagnosed?**	Overview of the tests/investigations that may be used to diagnose NAFLD
	**Understanding your health results**	What the different tests/investigations measure and what the results mean
	**NAFLD myths**	Common myths about NAFLD and why it shouldn’t be left unmanaged
	**Managing your NAFLD**	Animations demonstrating how lifestyle change can improve liver health, reduce cardiovascular disease risk and improve metabolic control
	**Patient success stories**	Real-life examples of how people with NAFLD or at risk of NAFLD have improved their liver health by making lifestyle changes
	**Long term heath complications from NAFLD**	Potential consequences of not managing NAFLD
**Module 3: Getting started with coaching**		How to access lifestyle coaches and what to expect from coaching sessions
**Module 4: Food and NAFLD**	**Energy balance**	How to balance energy requirements in the context of weight loss
	**Nutrition and NAFLD**	The relationship between diet quality, eating patterns and NAFLD
	**Understanding carbohydrates**	What are carbohydrates and the role they play in our diet
	**Understanding fats**	What are fats and the role they play in our diet
	**Understanding alcohol**	Recommended alcohol intake; calorie content in alcoholic drinks; provision of an online alcohol calculator
**Module 5: How do I make changes to my diet?**	**Finding the right dietary approach**	Animation explaining the evidence supporting two dietary approaches for managing NAFLD
	**Calorie restriction**	Calorie restriction in more detail; provision of online weight loss calculators and calorie checkers; link to the NHS weight loss plan
	**The Mediterranean diet**	Mediterranean diet in more detail
	**Other dietary approaches**	Information and external links to alternative dietary approaches
**Module 6: Practical tips**	**Supermarket tour**	Animation virtually walking the user around a supermarket providing practical tips on what to look out for when shopping and resisting temptation
	**Understanding food labels**	How to facilitate weight loss by understanding food labels
	**Portion sizes**	Recommended portion sizes of different food groups to promote weight loss and maintenance
	**Healthy eating recipes**	Provides external links to healthy eating recipes to promote weight loss and maintenance
**Module 7: Physical activity, exercise and NAFLD**	**How changing lifestyles contribute to NAFLD and weight gain**	Animation communicating how reduced physical activity levels are linked to weight gain and NAFLD
	**Combining physical activity and diet for weight loss**	The benefits of combining physical activity and dietary change to promote weight loss
	**Physical activity, exercise and NAFLD**	The difference between physical activity and exercise; how physical activity and exercise can benefit the liver and lead to other health benefits
	**How much physical activity do I need to do?**	The required amount, intensity and type of physical activity and exercise required to manage NAFLD; ideas for increasing physical activity and exercise levels
**Module 8: Steps to Success**	**Tips for setting your own goals**	Tips for setting SMART goals
	**Goal setting**	Tool to facilitate personalised behavioural goal setting for diet and physical activity
	**Set a food goal**	Tool to facilitate monitoring of diet against dietary goals
	**Step tracking**	Tool to facilitate monitoring of daily step counts and track progress
	**Weight tracking**	Tool to facilitate weight monitoring and track progress
	**Maximising chances of success**	Animation prompting use of SMART goals; self-monitoring and support from family and friends to maximise the chances of success

### VITALISE lifestyle coaching

As part of the VITALISE intervention, patients will have access to monthly personalised tele-coaching sessions delivered by trained lifestyle coaches. Coaches will have received training on what NAFLD is, how it is investigated, different treatment options (aligned with clinical guidelines) and the evidence supporting lifestyle intervention for the management of NAFLD in accordance with clinical guidelines. Coaches are also trained in the use of brief motivational techniques and will have an in-depth knowledge of the information content and self-regulation tools provided to enable signposting of patients during coaching sessions.

The initial coaching appointment will last approximately 20 min and subsequent appointments 10–15 min. Coaching duration and frequency were informed by findings from previously studies [15, 22]. The coaches will facilitate person-centred behavioural goal setting and encourage self-monitoring of lifestyle behaviours by using the tracking tools embedded within VITALISE.

### Additional support

A member of the research team will telephone each patient at the end of 12 weeks to answer any questions, promote continued engagement, and record any adverse events. Patients will be asked to self-report their weight, physical activity levels (step count and questionnaire) and complete the PAM.

Email reminders will be sent out to each patient once each week for the first four weeks, then monthly thereafter to prompt continued engagement with the intervention. Patients will have the opportunity to contact a member of the research team via telephone or email for assistance if they experience any technical difficulties during the study.

### Outcomes and criteria for success

Criteria to judge the feasibility of progressing to a larger scale evaluation:

#### Recruitment rate

Six patients recruited per month over a 6-month time period.

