#### Completion and follow-up rate

 ≥ 70% of those accessing the intervention providing data at 6-months follow-up.

These criteria aim to retain a sufficient sample size to determine acceptability and feasibility.

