#### Primary outcome measures

In line with NIHR guidance on feasibility studies, the focus will be to estimate important parameters that are needed to inform the design of a subsequent larger evaluation, if appropriate. Table 3 details the feasibility study parameters.

**Table 3 Tab3:** Feasibility study parameters

Parameter	Method of assessment
Recruitment rate	The number of eligible patients invited, who provide informed consent to participate in the study, versus those who decline, with reason(s) recorded
Intervention uptake, engagement and adherence	The number of patients who login to access VITALISE The mean and median number of times VITALISE is accessed over the 6-month time period
Completion and follow-up rate	The number of patients who complete the intervention, baseline and follow-up assessment outcome measures. Reasons for loss to follow-up will also be recorded

We will collect demographic data (age, sex, ethnicity, socio-economic status) on patients who decline to take part and record reasons for declining/unsuitability to inform the way in which the programme is promoted in the future.

Acceptability of VITALISE will be assessed qualitatively using in-depth, semi-structured interviews and all patients recruited will be invited to take part. Topics will focus on patients’ perceived expectations, benefits, motivations, and barriers to using/accessing VITALISE. These topics will be explored in relation to age and liver disease severity. We will qualitatively assess fidelity of receipt and enactment of the intervention to provide an indication of whether participants used the intervention as intended to make behavioural changes. Our interview topic guide will contain specific questions about each component of the intervention to determine whether they were received by participants and whether they utilised each component as intended. This information will inform optimisation of the intervention ahead of a large-scale evaluation, if appropriate. Those who drop out of the intervention will be invited to interview to explore reasons for drop-out. Findings will inform intervention optimisation.

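### The recruitment progression criterion (six per month for 6 months, 36 in total) does not match the target of 35 in 6 months, and no averaging or rounding rule says how 35 would be judged

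*Protocol article*

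**What the plan says.** The Sample size section of the protocol article states that "we will aim to recruit 35 patients over a 6-month time period". The Methods paragraph of the abstract gives the same figure: "The study aims to recruit 35 patients with newly diagnosed NAFLD over a 6-month time period".

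Under Outcomes and criteria for success, three criteria are introduced as "Criteria to judge the feasibility of progressing to a larger scale evaluation". The first, headed Recruitment rate, is "Six patients recruited per month over a 6-month time period". The other two (log-in, and follow-up among those accessing the intervention) are percentages written with a ≥ sign, at 80% and 70%. The recruitment criterion has no such sign. It does not say whether six is an average, a minimum for each month or a rounded figure. The purpose given for the criteria is that "These criteria aim to retain a sufficient sample size to determine acceptability and feasibility".

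Table 3, under Primary outcome measures, also lists a parameter called recruitment rate. Its method of assessment is "The number of eligible patients invited, who provide informed consent to participate in the study, versus those who decline", with reasons recorded.

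**The concern.** The target and the criterion describe the same recruitment over the same 6 months, so they should agree, and taken at face value they do not. The criterion helps decide whether a larger evaluation follows, so it should be possible to tell before any data are seen whether a given recruitment total passes. The total that matters most is the planned one, and that is where the wording leaves doubt. If recruitment ends at exactly 35 at the close of month 6, one reader could record a pass (5.83 rounds to 6) and another a narrow miss (35 is below 36), and nothing in the article settles it.

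A smaller matter is that one label serves two quantities. In the criterion, recruitment rate is a number of patients per month. In Table 3 it is a split between consenting and declining among those invited. The two can move apart: six per month can be reached with low consent if many patients are invited, and missed with high consent if few are eligible.

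**Working it through.** **Inputs, all from the protocol article**

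- Target: 35 patients in 6 months (Sample size; abstract, Methods).
- Criterion: 6 patients per month for 6 months (Recruitment rate).
- Later criteria: ≥ 80% of recruits log in; ≥ 70% of those accessing the intervention give 6-month data.
- No power calculation applies: "This feasibility study will not include formal hypothesis testing because it is not powered to detect clinically meaningful changes in outcomes".

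**Step 1. From the criterion to a total.** Total = rate × time = 6 × 6 = 36. The stated target is 35, so the gap is 36 − 35 = 1 patient.

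**Step 2. From the target to a rate.** Rate = 35 / 6 = 5.83 per month, which is 6 to the nearest whole patient. The shortfall against the literal criterion is 6 − 5.83 = 0.17 per month. As a ratio, 35 / 36 = 97.2%, or 2.8% short. The two figures therefore agree as a rounded rate but not as a literal threshold.

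**Step 3. When 35 patients would meet the rate.** At exactly six per month, 35 patients are reached in 35 / 6 = 5.83 months. A study that reaches 35 by then has recruited at six per month. The mismatch affects the case where the 35 patients take longer than 5.83 months, up to the full 6.

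**Step 4. Effect on the numbers the criteria are meant to protect.**

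| Recruited | Log in (× 0.80) | 6-month data (× 0.70) |
|---|---|---|
| 35 | 28.0 | 19.6 |
| 36 | 28.8 | 20.2 |

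The difference in expected follow-up is about 0.6 of a patient.

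**Step 5. How much the choice of reading matters.** The article gives no accrual model. As an assumption for illustration only, let accrual be Poisson with mean 35 over the 6 months, or 5.83 per month.

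- At least 35 in total: probability 52%.
- At least 36 in total: probability 46%.
- At least six in every one of the six months: 0.527 per month, and 0.527⁶ ≈ 2%.

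The first two differ only by the chance of exactly 35 patients, about 7%, so they restate the one-patient gap. The third shows that a strict month-by-month reading would be a very different test. The article does not adopt that reading, but its wording does not exclude it.

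**Step 6. Table 3.** The table counts the eligible invited patients who consent. Dividing that count by the 6 months of recruitment gives patients per month, and dividing it by the number invited gives the consent proportion. Both quantities are available from the planned data.

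**The case against.** The strongest reply is that there is no real conflict. The criterion carries no ≥ sign, unlike its two neighbours, and nothing says that six is an unrounded minimum, that 36 is required or that 35 fails. The natural reading is that it restates the target as a monthly rate in whole patients. The 35 is also an aim and not a stated cap, so recruitment could pass it. One patient changes expected follow-up by less than one person, and no hypothesis test depends on it. Most of this stands. Rounding is the likely origin of the figure, and the numerical effect is negligible. It does not supply the missing rule, though: a plausible explanation of how a threshold arose does not say how a result just under it is to be classed.

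A reader might go further and infer that a study meeting its target necessarily fails its own go criterion. The documents do not support that. It requires six to be an unrounded minimum and the 35 patients to take longer than 5.83 months.

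A reader might also infer that the Table 3 quantity cannot be compared with the criterion. It can, by one division. The CONSORT flowchart (Quantitative analysis) and the bi-weekly review of recruitment (Safety reporting) further indicate that the necessary counts will be available.

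Nor is the absence of a threshold for the consent proportion an error. The stated focus of the primary outcomes is estimation, and other entries in Table 3, such as the number of times the intervention is accessed, have no threshold either.

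**Conclusion.** The point holds as a small mismatch between a progression criterion and the planned sample size. The criterion implies 36 patients and the plan is for 35, a gap of one patient, 0.17 per month or 2.8%. Six is most plausibly 5.83 rounded, but since no rounding or averaging rule is stated, exactly 35 patients over the full 6 months would fall one short on a literal reading. This conclusion rests only on the article's own figures; the Poisson probabilities are illustrative and it does not depend on them. It does not threaten the study's validity, and it does not show that the criterion is unattainable.

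The double use of recruitment rate is a labelling point. It causes no loss of information.

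**What to change.** Restate the criterion as a total that matches the target: *at least 35 patients recruited within 6 months (average about 5.8 per month)*. The planned outcome is then clearly a pass, and both the month-by-month reading and the rounding question disappear.

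In Table 3, replace the single recruitment rate entry with two parameters: patients recruited per month, to be compared with the criterion, and the consent proportion among eligible patients invited, to be estimated without a threshold.

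The cost is wording only. No extra data, patients or analyses are needed. The change should be agreed and approved by the route given under Modification of the protocol, ideally before the recruitment total is known.
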